### Outcome Measures

A series of clinical, instrumented, and patient-reported outcome measures will be collected to characterize ankle-foot impairment, activity limitation, and participation restriction at baseline, during treatment, and longitudinally following treatment. Figure 2 shows the CONSORT flow diagram that details the study time points. The primary outcome of interest is improvement in patient-reported function on the FAAM. To help elucidate clinical improvement in function, we will assess if the intervention has shifted COP progression more medially during walking and if recurrence of subsequent ankle injuries has been reduced. Reinjury count data will be collected and assessed in both groups.

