### Patient-Reported Outcomes

The CAIT [23] is a 9-question instrument examining ankle pain and feelings of instability. The FAAM ADL and Sports subscales [24,25] and the Lower Extremity Functional Scale [26] assess difficulties in performing a variety of tasks. The NPRS [27] and Tampa Scale of Kinesiophobia [28] will be used to assess the participants’ pain and fear of movement due to the injury. Physical activity will be classified using the Godin-Shepard Leisure-Time Physical Activity Questionnaire [29] modified to record activity over the previous week rather than a typical week. These patient-reported outcomes will be recorded at all data collections (baseline, 2 interim sessions, discharge, and 6 postintervention follow-up assessments). Unstructured feedback requesting perceptions on participation in the uneven treadmill rehabilitation protocol will also be collected.

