### Statistical Analysis

To assess whether the addition of the rocky treadmill intervention to standard-of-care physical therapy improves rehabilitation, 4 repeated measurements of several outcomes (eg, CAIT and FAAM) will be measured over the active intervention period of the study. The data will be analyzed using an analysis of covariance–type linear mixed-effects model with Group, Time, and Group×Time variables as fixed effects and subject-specific variables {intercepts, slopes} as random effects. The null hypotheses for both LAS and CAI populations are that the slopes of the control groups equal those of the treatment groups.

To identify predictors and mediators of successful or unsuccessful rehabilitation outcomes, a 2-level (hierarchical) Bayesian model will be used to connect participant-specific responses to 6 explanatory variables: {X1, . . . , X6} = {age, sex, body mass index, pain intensity, weight-bearing status, and initial injury severity} to the subject-specific variables {intercepts, slopes}. A directed acyclic graph detailing the results of the Bayesian linear model will be developed (Figure 3). The regression parameters from the hierarchical Bayesian model will be estimated using Bayesian inference with Gibbs Sampling software, which creates a Markov chain Monte Carlo simulation of all regression parameters.

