To analyze the effect of the treatment on long-term reinjury rates between the 2 arms of the study, we will fit both logistic regression–type generalized linear mixed-effects (GLME) models to the data as well as Cox regression time-to-event models. The data that will be used in the analysis will be those obtained at baseline and during the postintervention period. In the GLME analysis, the response data will be (1) the self-reported survey instrument measure from the Patient-Reported Outcomes Measurement Information System and (2) the binary reinjury report (1/0). The GLME model will have Group, Time, and Group×Time as fixed effects and will use subject-specific variables {intercepts, slopes} as random effects. The null hypothesis of the GLME model is that the regression parameters associated with the Group and Group×Time effects are zero. In the Cox regression analysis, the response will be the time of suspension or the event along with a binary indicator of reinjury status, and the covariate will be Group. The null hypothesis of the Cox regression analysis is that the regression parameter associated with Group is equal to zero. In all analyses, a Bonferroni-type correction to the hypothesis test’s *P* values or α levels will be used to account for multiple testing.

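### The long-term model takes an unlisted PROMIS measure as its patient-reported response, under a logistic-type model, and no stated model covers FAAM at the six follow-up visits

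*Protocol article*

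**What the plan says.** All references are to the protocol article.

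- **Primary outcome (Outcome Measures).** "The primary outcome of interest is improvement in patient-reported function on the FAAM". No time window is attached.
- **Instruments (Patient-Reported Outcomes).** The section describes CAIT, FAAM ADL and Sports, LEFS, NPRS, the Tampa Scale of Kinesiophobia and the Godin-Shepard questionnaire. It then says: "These patient-reported outcomes will be recorded at all data collections (baseline, 2 interim sessions, discharge, and 6 postintervention follow-up assessments".
- **Hypothesis (Abstract, Objective; repeated in Discussion).** Patient-reported function is expected to be better in the experimental arm both directly after treatment and at 18 months.
- **Short-term model (Statistical Analysis).** The linear mixed model is introduced with "4 repeated measurements of several outcomes (eg, CAIT and FAAM) will be measured over the active intervention period of the study".
- **Long-term model (Statistical Analysis).** For reinjury after treatment, "we will fit both logistic regression–type generalized linear mixed-effects (GLME) models to the data as well as Cox regression time-to-event models". On the data: "The data that will be used in the analysis will be those obtained at baseline and during the postintervention period". The GLME has two responses. The first is "the self-reported survey instrument measure from the Patient-Reported Outcomes Measurement Information System"; the second is the reinjury report, marked as 1/0. The Cox response is time to reinjury.

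**The concern.** The long-term paragraph names a patient-reported response that appears nowhere else in the article, and it does not name the instrument the trial treats as primary. It also puts that response under a model type made for a yes/no outcome, with no rule for turning a score into one.

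The hypothesis about function at 18 months is at stake. An analyst following the text would look for a measure that is not on the list of collected instruments, and would find no instruction for the FAAM scores that are. The instrument, the model and possibly a cut-point would then have to be chosen later. If that happens after results by arm have been seen, the choice can depend on the results.

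**Working it through.** The question is settled mainly by setting sections side by side; the only arithmetic is a count.

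**1. Is PROMIS among the listed measures?**

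| Place in the article | PROMIS named? |
|---|---|
| Patient-Reported Outcomes (instrument list) | No |
| Figure 2 legend (instrument abbreviations) | No |
| Abbreviations | No |
| Statistical Analysis, long-term paragraph | Yes, without domain, form or scoring |

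**2. Which stated analysis uses FAAM after discharge?**

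| Stated analysis | Response | Period |
|---|---|---|
| Linear mixed model | Several outcomes, with CAIT and FAAM as examples | 4 intervention-period measurements |
| Hierarchical Bayesian model | Participant intercepts and slopes | Not stated; legend refers to healing rate |
| GLME, response 1 | PROMIS measure | Baseline and post-intervention |
| GLME, response 2 | Reinjury, 1/0 | Baseline and post-intervention |
| Cox model | Time to reinjury | Post-intervention |

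No row assigns follow-up FAAM to a model. The Bayesian model does not fill the gap: it serves the aim on predictors and mediators, and its six listed explanatory variables (age, sex, BMI, pain intensity, weight-bearing status, initial injury severity) do not include Group.

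**3. How many assessments are involved?**

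- Scheduled per participant: 1 baseline + 2 interim + 1 discharge + 6 follow-up = 10.
- Covered by the linear mixed model: 1 + 2 + 1 = 4, which matches its stated four measurements.
- Not assigned: 10 − 4 = 6.
- Ceiling over the trial: 312 × 6 = 1,872 records, with no attrition.
- With the article's 20% dropout, all taken before the first follow-up (an assumption, and the extreme case): 312 × 0.80 × 6 ≈ 1,498 records.

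**4. Does the model type suit the response?** A logistic model needs a binary response. The reinjury report is one. A questionnaire score is not, unless a cut-point is defined, and none is.

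**5. Is the sample size affected?** Power and Sample Size gives 62 per group for reinjury and allows 20% dropout: 62 / (1 − 0.20) = 77.5, rounded up to 78; 78 × 2 arms × 2 injury types = 312. Both stated figures reproduce. The FAAM figure of 17 per group relates to the intervention period. Neither calculation uses a long-term patient-reported outcome, so correcting that response changes neither.

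**The case against.** The strongest reply has four parts.

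**PROMIS may be collected, or may be a slip.** The article does not say that its instrument list is complete, and the Figure 2 image, which holds the schedule, is not available. PROMIS may have been left out of a condensed list, or the phrase may be a mistake for the collected patient-reported outcomes. This stands. A reader might infer that the trial will analyse a variable that does not exist; the article shows only that the variable is not listed. The need for correction survives both readings. If PROMIS is collected, the instrument list is wrong and follow-up FAAM still has no stated model. If it is a slip, FAAM may be included, but the text does not say which of the collected instruments is meant, so the number of tests for the planned Bonferroni-type correction is also open.

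**The full analysis plan may cover long-term FAAM.** It may, and silence alone would not be a finding. Here, however, the article does specify a long-term patient-reported response, and that response conflicts with its own instrument list.

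**The primary-outcome data are not lost.** A reader might infer that 60% of the primary-outcome data go unanalysed. The article does not support that. Outcome Measures sets no window for the primary outcome, and both the linear mixed model and the FAAM sample size refer to four intervention-period time points. On that window all the primary data are analysed. The six later assessments bear on the 18-month hypothesis.

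**GLME allows other links.** This is true of the model family, and the article gives no scale for the PROMIS measure. But logistic is the only type stated, both responses are placed under it, and only the second is marked as binary.

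**Conclusion.** The inconsistency is real. The patient-reported part of the 18-month hypothesis is tied to a measure absent from the listed instruments and to a model type suited to a binary response. FAAM at six of the ten scheduled assessments is assigned to no stated model.

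This rests on reading the article as written. If PROMIS stands for the collected instruments, the finding on FAAM softens from no stated model to an ambiguous response, while the model-type problem is unchanged.

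The reach is limited. The intervention-period FAAM analysis, the binary reinjury model, the Cox model and the sample size of 312 all stand. The article does not show that the 18-month FAAM data will go unanalysed; it shows that their analysis is not fixed in the text.

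**What to change.** In the long-term paragraph of Statistical Analysis:

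1. Replace the first GLME response with FAAM ADL and FAAM Sports.
2. Analyse these over baseline and the six follow-ups with a linear (Gaussian) mixed model, and state that the between-group difference at 18 months is the long-term contrast. How time is coded can stay the sponsor's choice. If the present Group, Time and Group×Time structure is kept, the contrast is the Group coefficient plus the Group×Time coefficient multiplied by the time value of the 18-month visit.
3. Reserve the logistic GLME for the 1/0 reinjury report.
4. If PROMIS is in fact collected, add it to Patient-Reported Outcomes and to the schedule, name the domain and scoring, give it a model with a suitable link, and still state the long-term FAAM model.

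The cost is a wording change in the protocol and analysis plan. The FAAM data are already scheduled, and no extra visits or participants are needed. The change should be made and dated before anyone sees outcome data by arm.

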**Objective:**

The aim of this study is to evaluate whether the inclusion of uneven treadmill training in standard rehabilitation can improve clinical, functional, biomechanical, and patient-reported outcomes compared with the standard of care alone in service members with LAS and CAI. The prophylactic effects of treatment on secondary injury and identification of any contributing or mediating factors that influence outcomes following treatment will also be evaluated. We hypothesize that service members receiving uneven treadmill training will demonstrate greater improvements in clinical and instrumented measures of impairment, patient-reported function, and lower risk of injury recurrence than the control group immediately post and 18 months following treatment.

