**Methods:**

A multisite, parallel randomized clinical trial will be performed among service members aged 18-49 years being treated for LAS and CAI in military treatment facilities in the United States. Participants randomly assigned and allocated to receive the experimental intervention will be provided up to 12 sessions of training on an uneven terrain treadmill over a 6-week treatment course to supplement standard rehabilitation care. Treatment intensity of the rehabilitation exercises and treadmill training will be progressed on the basis of patient-perceived intensity and treatment responses. Outcome measures will include patient-reported outcomes, functional assessments, performance measures, and biomechanical measures. Investigators collecting outcome measures will be blinded to treatment allocation. Reinjury rates and patient-reported outcomes of function will be tracked over 18 months following treatment.

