### Longitudinal Tracking of Reinjury

Injury count data derived following completion of the intervention will be employed to assess secondary preventive effects of the control and experimental treatments in the LAS and CAI strata. These follow-up data will be collected for 18 months. Both in-network and out-of-network medical care provided to service members will be captured by the MHS. Each recruiting site will conduct a chart review of the electronic medical record at the 6 posttreatment time points to assess for any additional medical care provided for ankle injuries in order to include physical therapy or surgical care. Participants will also be contacted directly to establish any secondary injury outcomes that were self-managed.

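### The long-term model of the self-reported measure fits a straight line from baseline to 18 months, which misdescribes a benefit gained during six weeks of training and loses power when that benefit fades

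*Protocol article*

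**What the plan says.** All references are to the protocol article. In Statistical Analysis, the long-term models take two responses. One is "the self-reported survey instrument measure from the Patient-Reported Outcomes Measurement Information System"; the other is a binary reinjury report. This point concerns the first only.

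- Data: "The data that will be used in the analysis will be those obtained at baseline and during the postintervention period". The on-treatment visits are left out.
- Terms: "The GLME model will have Group, Time, and Group×Time as fixed effects and will use subject-specific variables {intercepts, slopes} as random effects".
- Test: "The null hypothesis of the GLME model is that the regression parameters associated with the Group and Group×Time effects are zero". The article does not say whether this is one joint test or two separate ones.
- Visits (Patient-Reported Outcomes): "baseline, 2 interim sessions, discharge, and 6 postintervention follow-up assessments". Baseline plus six follow-ups gives seven time points. The text does not give the months of the follow-ups.
- Length of follow-up (Longitudinal Tracking of Reinjury): "These follow-up data will be collected for 18 months".
- Length of treatment (abstract, Methods): training is given "over a 6-week treatment course".
- Hypothesis (abstract, Objective): the experimental group is expected to do better on impairment and patient-reported function, with "lower risk of injury recurrence than the control group immediately post and 18 months following treatment". The two times close a list that includes patient-reported function.

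The article never calls Time linear in this model. It follows from giving each subject one intercept and one slope. The Figure 3 legend explains the same notation, for the Bayesian model, as a straight line fitted through each participant's responses. No visit factor, change point or baseline covariate is named for the long-term model.

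**The concern.** The treatment acts between baseline and the first follow-up, and nothing is delivered afterwards. The group difference therefore starts at zero, steps up during treatment, and then holds or fades. The planned model allows only a difference that starts at some value at baseline and changes by a constant amount per month to 18 months.

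Three things follow. If Time counts from baseline, the Group coefficient is the fitted gap before treatment, which randomisation makes zero in expectation, so it has no treatment meaning. The fitted gap at 18 months, one of the two hypothesised times, is biased. And a fading benefit can give a zero or negative Group×Time, which invites the reading that training did nothing or did harm. At stake are the power and the interpretation of the trial's long-term claim on patient-reported function.

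**Working it through.** **The plan's own figures.** Power and Sample Size gives 62 per group, inflated for 20% dropout: 62/0.8 = 77.5, so 78; 4 × 78 = 312. Both reproduce. They belong to the reinjury response; the article gives no power for the long-term self-reported response. I borrow 62 per group (one injury stratum).

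**Assumed inputs, not in the documents.** Continuous response with identity link; SD 10 at baseline; share ρ of that variance between subjects, 0.4-0.6; random-slope SD 0.2 per month; complete data; two-sided 0.05 before any Bonferroni step; follow-ups at 3, 6, 9, 12, 15, 18 months or at 1, 3, 6, 9, 12, 18 months. True differences: 4 points held; 4 fading linearly to 2 from first to last follow-up; 6 fading likewise to 1.

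**Method.** Let V be the 7 × 7 covariance of one subject's values, with entries 100ρ + 0.04·s·t, plus 100(1−ρ) on the diagonal. Let X have columns 1 and t, and let d be the true difference at the seven times (d = 0 at baseline). The planned model estimates b = (X′V⁻¹X)⁻¹X′V⁻¹d, with covariance (2/62)(X′V⁻¹X)⁻¹. The two elements of b are Group and Group×Time.

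**One case in full: ρ = 0.5, three-monthly visits, 4 points held.**
- Group = 2.14 (SE 1.537) and Group×Time = 0.143 per month (SE 0.0877). The fitted gap is 2.1 at baseline (truth 0) and 2.14 + 18 × 0.143 = 4.7 at 18 months (truth 4).
- Power: Group 29%, Group×Time 37%, joint 2-df test (non-centrality 8.00) 72%.
- Visit-based change contrast, mean of six follow-ups minus baseline: variance 50 + 50/6 + 0.04 × 10.5² = 62.74; SE = √(62.74 × 2/62) = 1.423; 4/1.423 = 2.81; power 80%.
- Same mean, baseline as covariate: 62.74 − 50²/100 = 37.74; SE = √(37.74 × 2/62) = 1.103; 4/1.103 = 3.63; power 95%.

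**All settings (three values of ρ, two schedules).**

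| | 4 held | 4 to 2 | 6 to 1 |
|---|---|---|---|
| Fitted gap at baseline (truth 0) | 2.1-2.7 | 2.4-2.7 | 3.8-4.2 |
| Fitted Group×Time per month | 0.11 to 0.14 | 0.00 to 0.02 | −0.12 to −0.08 |
| Fitted gap at 18 months (truth) | about 4.7 (4) | 2.7-2.8 (2) | 2.0-2.3 (1) |
| Power, Group alone | 27-48% | 32-50% | 65-85% |
| Power, Group×Time alone | 22-43% | 5-6% | 14-32% |
| Power, joint test | 65-75% | 32-46% | 55-77% |
| Power, change contrast | 73-89% | 49-71% | 62-87% |
| Power, baseline-adjusted | 95-97% | 77-86% | 88-96% |

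**A larger effect.** With a 0.5 SD benefit, between-subject share 0.5-0.7, slope SD 0-0.03 SD per month and three schedules, a held benefit has 82-95% joint power, or 58-77% if the two coefficients are tested separately at 0.025. If it fades by half, joint power is 40-59%, against 81-98% for the baseline-adjusted mean.

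**The case against.** **The null names both coefficients.** A reader might infer that a held benefit is likely to be missed, by setting 37% for Group×Time alone against 80% for the change contrast. The documents do not support that. The stated null covers Group and Group×Time, most naturally as a joint test; a null on slopes alone belongs to the intervention-period model. Jointly, the case worked in full loses 72% against 80%, about 8 points, and at ρ = 0.4 the joint test and the change contrast are about equal. Much of the gain to 95% comes from baseline adjustment, not from the shape of Time. All of this stands.

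**The model form is partly inferred.** The article does not say that Time is linear, where it starts, or that baseline is a response. If baseline were a covariate and only follow-ups were modelled, a held 4-point benefit would be recovered (Group 4.0, Group×Time 0) with 91-95% joint power. That would remove the problem for a held benefit, but it is not what is written: baseline is listed among the data analysed and no covariate is named for this model. Moving the origin of Time would change what Group means, but not the fitted lines, the joint test or the sign of Group×Time.

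**The model is not wholly misleading under fading.** A positive Group with a negative Group×Time does describe an advantage that narrows, and in the 6-to-1 case Group×Time is significant in only 14-32% of trials. That is fair. But the narrowing is measured from a pre-treatment gap that does not exist.

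**The time just after treatment is covered elsewhere.** The intervention-period model includes discharge. I accept this, and ask for no such contrast here.

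**Conclusion.** The point holds as a mismatch between model and expected pattern, not as a finding that a lasting benefit would usually go undetected. On the most natural reading, the model gives a Group coefficient without treatment meaning, a biased 18-month difference (0.7 points too high for a held 4-point benefit) and a Group×Time whose sign can run against the treatment. A held benefit is usually detected by a joint test (65-75% at 4 points, 82-95% at 0.5 SD). At 4 points it is likely to be missed only if Group or Group×Time is read alone (27-48% and 22-43%). The clearest loss is under fading: 32-46% jointly for 4 to 2 points, against 49-71% for a change contrast and 77-86% with baseline adjustment.

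The direction of these errors follows from the model and a six-week treatment. Their sizes rest on the assumed effect, SD, correlations, slope variance and visit months. A Bonferroni step would lower the power figures. The point does not extend to the reinjury response or to the choice of instrument.

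**What to change.** For the long-term self-reported measure only:

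1. Use the baseline value as a covariate, or keep it as a response with a common baseline mean for both groups.
2. Enter follow-up visit as a six-level factor with Group×visit.
3. Replace the null on Group and linear Group×Time with two named contrasts: the group difference averaged over the six follow-ups, and the difference at 18 months.

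A slope over the follow-up visits can stay as description. The data and visits are unchanged; only analysis wording changes.

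Costs: a few more mean parameters and two tests that may share alpha. In the case worked in full, the averaged contrast at 0.025 still has power Φ(3.63 − 2.24) = 92% for a held benefit; for 4 to 2 points it has Φ(3/1.103 − 2.24) = 68%, against 36% for the joint test at 0.05. The 18-month contrast is weaker: variance 50 + 0.04 × 18² + 50 − 25 = 87.96, SE √(87.96 × 2/62) = 1.684, and power for 4 points at 0.05 is 66%. Some power is also lost if the benefit truly grows linearly. For growth to 0.5 SD (share 0.5, slope SD 0.03 SD per month, the two schedules above), Group×Time has 78-79%, the averaged contrast 57-71% and the 18-month contrast 76%.
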